### MRI protocol

We will perform several MRI sequences before and after the CCT to assess functional and structural brain changes. Imaging data will help identify elements of restoration and compensation in task related brain activity after the CCT [51, 52]. Two fMRI tasks will be performed in this study. The first task will be an adapted version of a face-occupation task described in a previous study [53] to assess EM, while the second one is an adapted version of a task to assess spatial abilities (SA) [54]. In the face-occupation task, the association between face and occupation pairs has to be learned during the encoding phase. During the control condition, head contours are displayed and participants have to indicate, if the head contour belongs to a male or female. In the cued recall condition, the previously encoded faces are shown again and the question whether the occupation requires a university degree or an apprenticeship has to be answered. During the recognition condition, the faces are presented with two occupations and participants have to indicate which occupation is associated with the face. We expect activity in the medial temporal lobe and occipital brain areas as a previous study with a very similar paradigm showed activity in these brain areas. While the activity in the MTL is expected in EM tasks, the occipital activity might be caused through the task design, where different stimuli were used in the control than in the other conditions (i.e., pictures of faces vs head contours) [55]. In the SA task, participants are asked to mentally translate or rotate two puzzle pieces to indicate if they fit together to build a square. As control condition, two grey squares are presented in similarly shaped puzzle pieces. The participants are asked to indicate if both grey squares have exactly the same color. Based on previous results in the spatial abilities task, we expect activity in the superior parietal cortex bilaterally, the left inferior parietal cortex, bilateral lateral occipital cortex and the medial frontal gyrus. These brain areas are associated with complex visual-spatial construction tasks [54]. Please see the supplementary material for a detailed description of the fMRI tasks (see Additional file 2).

In the analysis of task fMRI, we will predefine regions of interest (i.e., regions with significant activity in the baseline assessment) and investigate how these areas change activity through the training. Additionally, we will also perform whole brain analyses to find new clusters of activity not present in the baseline assessment as a possible sign of compensatory activity [48]. Scanning at both study sites will be performed with 3 Tesla scanners (Bern: Siemens Magnetom Prisma, 32 channel head coil; Lucerne: Siemens Magnetom Vida, 64 channel head coil). From all participants, T1- weighted images (MP2RAGE, TR = 5000 ms, TE = 2.98 ms, TI 1/2 = 700 ms/2500 ms, flip angle 1/2 = 4 degrees/5 degrees, FOV = 256, matrix = 256 × 256, voxel size = 1 × 1 × 1 mm, 176 slices) will be acquired. For the fMRI sequences we will acquire echo-planar imaging (EPI) with 360 (resting state fMRI), 604 (SA Task) and 638 (EM task) volumes (TR = 1000 ms, TE = 37 ms, flip angle = 30 degree, FoV = 230 mm, matrix = 92 × 92, accelerating factor 8, voxel size 2.5 × 2.5 × 2.5 mm, 72 slices). Furthermore, we will perform an ASL sequence (91 volumes, TR = 3300 ms, TE = 13 ms, Flip angle = 90 degree, FoV = 230 mm, matrix = 64 × 64, voxel size 3.6 × 3.6 × 6.0 mm, 22 slices).

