#### Neuroimaging

One crucial part to in-depth understanding of CCT effects and mechanisms is situated in its’ physiological and more specifically neuronal correlates. Several studies have combined cognitive training with magnetic resonance imaging (MRI) to investigate neuronal changes resulting from cognitive training [24, 25]. Imaging can be employed to demonstrate target engagement and underlying mechanisms by measuring brain changes over the intervention period [26]. Here, functional MRI (fMRI) can help to distinguish changes in the network underlying the task specifically trained (e.g., hippocampus in an episodic memory task) from changes in neuronal processing observable outside the task-specific network where they may play a compensatory role. Data on functional brain changes due to CT showed increased as well as decreased activity after the CT [27]. However, these differing findings are probably caused by the complex relationship between task performance and changes in brain activity. If increased brain activity after CT is associated with increased task performance, this might indicate successful compensatory brain activity [28]. Stable performance in combination with decreased brain activity after CT on the other hand might indicate more efficient task processing as a consequence of the CT.

In summary, possible task fMRI results indicating beneficial CT in older adults at risk of AD are:I.Decrease in task-related brain network activity after CT and constant task performance as a consequence of more efficient task processingII.Decreased activity in brain regions outside the task-related network because brain regions within the task-related network are more active againIII.Increased activity in previously hypoactive task-related brain network and increased task performance through CT (restoration)IV.New activity in brain areas not active before CT (new compensatory activity) and increased task performance

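### Task-fMRI regions are chosen by baseline significance with no independent definition of the task network, so restoration can be read as compensation and the decline of a compensatory region as efficiency

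*Protocol article*

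**What the plan says.** The Neuroimaging section of the Introduction lists four task-fMRI patterns that would indicate a beneficial training:

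- **I:** less activity in the task-related network with constant performance (efficiency).
- **II:** less activity outside that network, because the network itself is working again.
- **III:** "Increased activity in previously hypoactive task-related brain network and increased task performance through CT (restoration").
- **IV:** "New activity in brain areas not active before CT (new compensatory activity) and increased task performance".

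The same section says fMRI can separate change within the trained task's network from "changes in neuronal processing observable outside the task-specific network where they may play a compensatory role".

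The MRI protocol section states the aim: "Imaging data will help identify elements of restoration and compensation in task related brain activity after the CCT". It gives two analysis steps. The first is to "predefine regions of interest (i.e., regions with significant activity in the baseline assessment") and follow how these areas change with training. The second is a whole-brain analysis to "find new clusters of activity not present in the baseline assessment as a possible sign of compensatory activity".

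That section also states expectations from earlier studies. For the episodic memory (EM) task: "We expect activity in the medial temporal lobe and occipital brain areas", with the remark that the occipital part may come from using different stimuli in the control condition. For the spatial abilities (SA) task: "we expect activity in the superior parietal cortex bilaterally, the left inferior parietal cortex, bilateral lateral occipital cortex and the medial frontal gyrus". Neither list is made the region-of-interest set or a rule for network membership.

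**The concern.** Patterns III and IV both carry improved performance, so performance cannot separate them. What is left is whether the region belongs to the task network. Patterns I and II are likewise distinguished by location, inside or outside the network. The analysis rule, however, sorts regions by whether they were significantly active at baseline in a sample that runs from subjective cognitive decline to mild AD. Network membership and baseline significance are different properties, and they diverge in the two cases of most interest: a network region that is strongly under-active, and a non-network region already recruited to compensate.

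At stake is the mechanism that is reported. If the label follows the baseline threshold, restoration can be published as compensation, and a fading compensatory response as a more efficient network. Without a prior rule, the label can also be chosen after the results are seen.

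**Working it through.** The point concerns definitions, and the article states no figure for it. The passages are set side by side first; the arithmetic then shows how often the first type of mislabelling could arise.

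**1. Where each type of region goes under the stated rule**

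| True status of region | Baseline | Assigned to | Change after training | Reading open under the rule |
|---|---|---|---|---|
| Network | above threshold | region of interest | decrease | efficiency (I), correct |
| Network, mildly under-active | above threshold | region of interest | increase | restoration (III), correct |
| Network, strongly under-active | below threshold | whole-brain search | increase | new compensation (IV) instead of III |
| Outside network, not recruited | below threshold | whole-brain search | increase | new compensation (IV), correct |
| Outside network, already recruited | above threshold | region of interest | decrease | efficiency (I) instead of II |

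Rows three and four look the same to the rule, as do rows one and five. The row-five error does not depend on low power: the stronger the baseline compensation, the surer the region's entry into the region-of-interest set.

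**2. How often a network region falls below threshold (row three)**

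Inputs:
- n = 162 baseline scans, or 54 for one arm (Sample size section). Neuroimaging at baseline is planned in all arms (Fig. 1 legend). Pooling all arms is the favourable case.
- d = group mean activation divided by its SD at baseline. Assumed; the article gives none.
- Threshold: one-sided p<0.001 uncorrected, or t = 4.8 as a stand-in for a corrected threshold. Both are assumed; the article gives none.

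Formula: one-sample t with n − 1 degrees of freedom and noncentrality d√n. The probability of missing the region-of-interest set is P(t < cut-off).

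For n = 162, √162 = 12.73 and the p<0.001 cut-off is t = 3.14. For n = 54, √54 = 7.35 and the cut-off is t = 3.25.

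| d | Noncentrality, n=162 | Miss, n=162, p<0.001 | Miss, n=162, t=4.8 | Miss, n=54, p<0.001 |
|---|---|---|---|---|
| 0.20 | 2.55 | 72% | 98% | 95% |
| 0.25 | 3.18 | 48% | 94% | 91% |
| 0.30 | 3.82 | 25% | 83% | 84% |
| 0.40 | 5.09 | 3% | 39% | 61% |

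A normal approximation, Φ(3.09 − d√162), agrees closely: 71%, 23% and 2% at d = 0.2, 0.3 and 0.4.

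These are probabilities that a region is left out of the region-of-interest set. They are not probabilities of a wrong label, which also requires that the region recovers and that it is then interpreted without regard to the expected anatomy.

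**The case against.** Several points on the other side are sound.

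- Pattern IV is worded as areas not active before training, and the whole-brain step follows that wording closely. The analysis section does not simply replace the Introduction's criterion. Still, the Introduction places compensation outside the task network, and pattern III covers a network that was under-active before training, so a sub-threshold network region fits III and IV at once.
- The article does not call the regions of interest the task network, and it does not say that a decline in them will be read as efficiency. New clusters are only a possible sign of compensation. This hedge stands, but no criterion is offered for deciding otherwise.
- Under-active does not mean non-significant. Regions still above threshold stay in the set, and with 162 scans at p<0.001 a region at d = 0.4 is almost never missed.
- Patterns I and II differ in more than location: I requires constant performance, and II comes with a rise inside the network. Reading these jointly helps, but the rise can only be recognised if the network has been defined.
- The stated task-fMRI hypotheses (Objectives) concern efficiency, which baseline-active regions address directly. Imaging is secondary, and the third objective is exploratory.
- Detail on regions of interest is often left to an analysis plan. Here, though, the article states the selection rule outright.

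A reader might infer that the plan defeats its own aim, or that every recovering region will be reported as compensation. The documents do not support either. The labels are hedged, only sub-threshold regions are misfiled, the whole-brain search keeps those regions in view, and the expected regions offer an anatomical reference that an interpreter could use.

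**Conclusion.** The concern holds in a limited form. The plan sorts regions by baseline activation in its own participants and gives no independent test of network membership, so III can be read as IV and II as I. This weakens the secondary aim of identifying restoration and compensation; it does not make that aim unattainable, and it leaves the cognitive outcomes alone.

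The size of the first error rests on assumed values of d and of the threshold. It is likely for strongly under-active regions (72% left out at d = 0.2 with 162 scans at p<0.001), moderate at d = 0.3 (25%) and negligible at d = 0.4 (2–3%). It is larger under a stricter threshold or if regions are selected within one arm. The second error has no comparable figure: it depends on how many compensatory regions are already active at baseline, about which the article gives no information.

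**What to change.** Keep the baseline-active regions of interest and the whole-brain search, and add a network reference that does not depend on this sample's activation:

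1. Before follow-up maps are examined, define each task's network from the prior-work regions in the MRI protocol section. For EM, use the medial temporal lobe, with occipital areas handled separately because the article itself attributes them possibly to the control stimuli. For SA, use bilateral superior parietal, left inferior parietal, bilateral lateral occipital and medial frontal regions.
2. Classify every region-of-interest change and every new cluster as inside or outside that network before calling it restoration, efficiency or compensation.
3. Read the label jointly with task performance and, for a decrease outside the network, with whether activity inside it has risen.

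Replacing the baseline functional regions entirely by anatomical masks is not necessary and would be a debatable trade.

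The cost is some wording in the analysis plan, a set of masks and a little more analysis; no new scans. The drawback is that a network list taken from earlier work may be incomplete, or broader than the activation peaks and so dilute regional averages. The list should therefore be reported with the results.

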### Blood analysis

Blood samples will be taken once during the first group session. Genotyping for BDNF ApoE will be performed. Furthermore, plasma pTau181, Amyloid Beta_42_, Amyloid Beta_40_, glial fibrillary acidic protein and neurofilament light will be analyzed to estimate AD related brain pathology [38–40].

### Outcomes

Each participant will perform the cognitive assessments four times in intervals of approximately 10 weeks. The individual cognitive profile will be assessed through a set of paper-pencil and tablet-based cognitive tests designed to evaluate typical AD components. More precisely, the general cognitive performance will be assessed in a paper-pencil version of the MoCA. The following tests will be administered as tablet-based versions: the auditory verbal learning test (AVLT) [56] to assess episodic memory, the Rey-Osterrieth Complex Figure Test (ROCF) [57] for spatial abilities/memory, and verbal fluency as well as the Graded Naming Task (GNT-30) [58] will be used to probe semantic memory. Additionally, participants will performed the Flanker Test [59] to assess attention/response inhibition abilities and the digit span test (forward and backwards) as measure of short-term memory and working memory respectively. Parallel versions of the tests will be used whenever possible. Based on this comprehensive test battery, a cognitive composite score will be calculated as primary outcome of cognitive performance.

Moreover, participants will be asked to complete questionnaires to assess their form of the day, their situational motivation [60], quality of life [61] and depressive symptoms trough the geriatric depression scale (GDS) [62]. Through in-house designed or adapted questionnaires, participants’ expectancy towards the cognitive training (Additional file 3) [63], and subjective cognitive performance (Additional file 4) will be assessed. Subjective cognitive performance will additionally be assessed in an informant rated version of the questionnaire (filled out by a close friend or relative) (Additional file 5). Unexperienced participants will have the opportunity to get used to the tablet and to have one on one support from the investigator before the training starts.

The mentioned tests will be supplemented by a set of paper-pencil based questionnaires that will be sent to the participants before the first on-site meeting. These preliminary questionnaires asses activities of daily living [64], handedness [65], and the informant rated subjective memory performance questionnaire.

### Statistical methods

#### Sample size

For our primary analysis (“Does change in performance on the three typical AD domains 3 months after the start of the training differ between groups?”), a repeated- measures ANOVA is planned (3 groups with 2 time points). We computed the necessary sample size using G*Power [66] to ensure a power of 80% to detect an assumed moderate effect (i.e. effect size: η2 = 0.06, f = 0.25) with α of 5%. The power analysis revealed a total sample size of 162 (54 participants per group). Moreover, we performed a power analysis for testing the interaction between the groups and all four time points within a repeated-measures ANOVA using the same parameters as before (α = 5%, power = 80%, η2 = 0.06) as well as a non-sphericity correction factor of 0.75. According to this power analysis a total sample size of 96 (32 participants per group) is needed.

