### Objectives

The main objective of this study is to train cognitive domains typically affected by AD through a serious game-based CCT and to assess the training effect on cognition and neural parameters of older adults in an at-risk or manifested stage of AD relative to an active and a waitlist control group. We set out to combine direct training of episodic memory, semantic, and spatial abilities with working memory training to facilitate transfer to every-day functioning. By combining group- and at-home based training elements, while integrating collaborative social elements both within the app as well as during the group sessions, we expect high adherence. In summary, the purpose of this study is 1) to investigate the effectiveness of our CCT on the three cognitive domains typically affected in AD, 2) investigate transfer effects and 3) to explore the neuronal underpinnings of the CCT.

We hypothesized that participants enrolled in the CCT group will show larger and more durable improvements in cognitive performance after training compared to those in either the active control group or the waitlist control group. We expect changes in functional brain activity to be observed during rest (i.e., increased connectivity in the DMN/CEN and increased CBF). Based on the findings reported in the previous section [10], we also expect increased functional connectivity between the hippocampus and frontal as well as temporal brain areas. In task fMRI, we expect indications for more efficient task-specific networks. When keeping the number of solved trials constant (e.g., in an externally paced task protocol) we expect declining activity due to higher task efficacy in the intervention group. In the self-paced SA task, we expect more solved trials in all participants but less activity increase in task-related networks after training compared to baseline activity. This finding would again reflect more efficient networks [28]. Furthermore, we aim to identify factors that moderate the magnitude of these effects. As shown in our previous cognitive training study [41], participants with less advantageous cognitive profiles at baseline, particularly, may benefit from cognitive interventions. Other factors which might moderate training benefits are blood and genetic markers like ApoE 4 genotypes and plasma amyloid which will also be analyzed during this study.

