### Explanation for the choice of comparators: active control group and waitlist control group

To test whether potential improvements in the intervention group result specifically from the training and not just from e.g. meeting as a group or performing an activating task, we use an active control group. To match the at-home element of the intervention group participants in the active control group will be asked to watch documentaries on the tablet computer matched for time and frequency of the CCT. To ensure that the participants are attentively watching the videos, pop-up windows with easy to solve multiple choice questions (e.g. “What is 2+3?”) randomly appear during the documentaries sessions. This active control condition aims to include the same level of social interaction in a group setting again matched for duration and frequency but without explicit cognitive training. To this end, participants are asked to discuss the documentaries with the other group members. Additionally, participants will play group games that are not cognitively demanding and where success is based on chance rather than skill (e.g., Bingo in slow speed). The active control intervention lasts 10 weeks. Afterwards, participants perform the same CCT as the intervention group.

Before staring the CCT, the wait-list control group will have a 10-week passive waiting period after the first cognitive assessment and MRI scan. The waitlist control group will allow us to quantify test-retest effects as well as habituation to the MRI scanner setting as in previous work by others [48].

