#### Statistical methods for primary and secondary outcomes

Primary outcomes are three composite scores corresponding to the domains mostly affected by AD. One advantage of composite scores is a reduced number of statistical tests. At the same time, separate composite scores for the three domains allow to assess and compare changes in the scores individually. For each of the domains, three variables will be included in the composite score (EM: AVLT learning sum, immediate and delayed recall; SA: ROCF encoding, immediate and delayed recall; semantics: semantic fluency from the MoCA, phonemic fluency and GNT). We will perform a principal component analysis (PCA) for each of the respective domains.

All scores will be scaled and centralized on the scores from the baseline assessment and weighted if appropriate according to their loadings in the PCA. The main hypothesis will be tested with a repeated-measures ANOVA for which an adequate level of power should be guaranteed (according to the power analysis described before). Further analyses (using all time points and additional numeric subject characteristics as predictor variables) will be performed with linear mixed models as they allow for more sophisticated model design and a better handling of missing data. As covariates, the factors study site and study arm will be included in all analyses. Neuroimaging data will be analyzed with SPM12 and related toolboxes (e.g., Functional Connectivity (CONN) toolbox [67]). Apart from task related fMRI, resting state fMRI, volumetrical images and ASL will be performed.

To assure meaningful data, non-adherence to the training regimen leads to exclusion of further analysis. Non-adherence is defined as completing less than 50% of the required training sessions and attendance of less than 70% of the group sessions.

Given that a relatively high number of games are purposely built for this study, we expect the need for continuous adjustments based on feedback from participants. Should substantial adjustments be necessary, we will introduce release number as a covariate in the analysis.

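### The primary three-arm F test is not sufficient to establish that CCT beats its controls, and the stated 80% is power for that omnibus test only

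*Protocol article*

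**What the plan says.** Under Objectives, the protocol article expects the CCT group to show "larger and more durable improvements in cognitive performance after training compared to those in either the active control group or the waitlist control group". The section on the choice of comparators gives the active control its purpose: "To test whether potential improvements in the intervention group result specifically from the training and not just from e.g. meeting as a group". It gives the waitlist a different task, which is to quantify retest effects and habituation to the scanner.

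Under Sample size, the primary question is "Does change in performance on the three typical AD domains 3 months after the start of the training differ between groups", and "a repeated- measures ANOVA is planned (3 groups with 2 time points"). The assumed effect is η² = 0.06, f = 0.25, with α of 5% and power of 80%, and the result is given as "The power analysis revealed a total sample size of 162 (54 participants per group").

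The section on statistical methods for primary and secondary outcomes then ties hypothesis to test: "The main hypothesis will be tested with a repeated-measures ANOVA for which an adequate level of power should be guaranteed". The primary outcomes are three domain composites. Neither of the two statistical sections names a contrast of CCT with the active control or with the waitlist.

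**The concern.** The hypothesis has a direction and concerns two named comparisons. The test assigned to it has no direction and concerns all three arms at once. Its null hypothesis is that the three mean changes are equal, so it can be rejected because the waitlist lags, because the documentaries arm does best, or because CCT does worst. None of these supports the hypothesis.

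Two things are at stake. First, a significant F could be read as confirming the main hypothesis without evidence that training adds anything to group contact and activation, which is the question the active control was included to answer. Second, the stated 80% may be taken as the chance of detecting a training-specific benefit. The sample size was not derived for that comparison.

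**Working it through.** **Inputs from the article:** three arms, two time points, f = 0.25 (η² = 0.06), α = 0.05, power 80%, N = 162, n = 54 per arm. **Scale:** the SD of the change score is set to 1, so all gaps are in SD of change.

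**1. Reproduce the plan's figure.** With two time points, the group-by-time test is an F test on 2 and N − 3 degrees of freedom. With noncentrality λ = f²(N − 3):
- N = 162, f = 0.25: λ = 0.0625 × 159 = 9.94, power 80.5%. The smallest N reaching 80% is 161, which is 162 in equal arms. The stated size reproduces.
- Using η² = 0.06 directly: f² = 0.06/0.94 = 0.0638, λ = 10.15, power 81.4%.
- The article's second figure (96, four time points, correction 0.75) also reproduces under the same convention, with power 81.3%.

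**2. Translate f into arm differences.** λ = n Σ(μᵢ − μ̄)², so power depends on the spread of the three means and not on which arm differs.
- One arm apart from the other two by d: Σ = (2/3)d², λ = 36d², so d = √(10.15/36) = 0.53.
- Evenly spaced arms with total range D: Σ = D²/2, λ = 27D², so D = √(10.15/27) = 0.61. Neighbouring arms are then 0.31 apart.

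**3. What the omnibus test does under different patterns** (100,000 simulated trials each, 54 per arm, pairwise test two-sided 5% with pooled variance on 159 df):

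| CCT / active / waitlist | Omnibus F significant | CCT significantly above active |
|---|---|---|
| 0.53 / 0 / 0 | 81.3% | 78.2% |
| 0.53 / 0.53 / 0 | 81.4% | 2.5% |
| 0 / 0.53 / 0 | 81.5% | 0.0% |
| −0.53 / 0 / 0 | 81.3% | 0.0% |
| 0 / 0 / 0 | 5.0% | 2.6% |

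If CCT equals documentaries and the gap to waitlist is smaller, rejection falls. At 0.3 SD, λ = 36 × 0.09 = 3.24 and the rejection probability is 34%.

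**4. Power for the comparisons in the hypothesis.** For a pairwise gap δ, the noncentral t has parameter δ√(n/2) = δ√27.
- δ = 0.53 (CCT alone gains): 0.531 × 5.196 = 2.76, power 78%.
- δ = 0.31 (evenly spaced): 0.307 × 5.196 = 1.59, power 35%. Reaching 80% would need about 168 per arm.
- CCT significantly above both controls when CCT alone gains 0.53 SD: 66% by simulation. Reaching 80% would need about 70 per arm, or 210 in total.

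**The case against.** The strongest defence has three parts.

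*An omnibus F is a legitimate gate.* With exactly three groups, unadjusted pairwise tests made only after a significant F hold the family-wise error at 5% per outcome. Follow-up contrasts are commonly left to an analysis plan, and none is shown here. This stands as far as it goes: the article cannot be faulted for omitting contrast details. But it goes further than omission. It states the primary question, the test, the link from hypothesis to test and the basis of the sample size, and the stated test does not match the stated hypothesis. Contrasts in an unseen plan would not change what 162 was sized for.

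*The 81% is not an error rate for a training claim.* A reader might infer that the test rejects with 80% probability whenever CCT is no better than documentaries, or that a false training claim has that probability. The article supports neither. The 81% requires both arms to exceed waitlist by about 0.53 SD, and in that case rejecting equality of the three arms is correct. A direct CCT-over-active contrast is then significant in only 2.5%. Nor does the article say that a significant F will be reported as a training-specific effect.

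*The power criticism depends on the pattern.* The article gives f but not the arrangement of the means. If CCT alone gains, the pattern closest to the hypothesis, each contrast has 78% power, close to the nominal 80%. The 35% comes from an assumed even spacing. That assumption is reasonable, because the comparator section itself allows that group meetings or an activating task might produce gains, but it remains an assumption.

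The wording of the hypothesis (either control) is also loose. On any reading, however, it is directional and the F test is not.

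**Conclusion.** The mismatch is real and should be fixed. The group-by-time F test is not sufficient to establish the directional hypothesis, and the 80% describes only the omnibus test. At the planned effect size the omnibus test rejects in about 81% of trials whether CCT alone gains, CCT and documentaries gain equally over waitlist, or CCT does worst.

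Power for the active-control comparison lies between about 78% (CCT alone gains 0.53 SD) and about 35% (evenly spaced arms, gap 0.31 SD), and power to beat both controls is about 66% in the favourable case. These figures assume complete data on 54 per arm, equal variances of change and two-sided 5% tests.

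It would go too far to call the sample-size calculation wrong. It reproduces under a standard convention.

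**What to change.** Within each domain composite, make the confirmatory tests planned contrasts on change from the first to the second assessment, in a fixed order stated in advance and each at two-sided 5%: for example, CCT minus waitlist, then CCT minus active control. State that any training-specific claim requires the CCT-minus-active contrast. Keep the omnibus F as supportive. In the sample-size section, label the 80% as omnibus power and add the pairwise figures (78% at 0.53 SD, 35% at 0.31 SD) and the joint figure (66%). Settle this before change scores are examined by arm.

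The order should be chosen knowingly. With waitlist first, the active-control claim needs both contrasts, so the 66% applies to it in the favourable pattern. With active control first, its own 78% applies.

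The cost is text only: no arm, visit or measure changes. The price is a less favourable stated power for the active-control comparison. If 80% to beat both controls were wanted, the size would be about 210 rather than 162. The sequence controls error within one domain only. Three composites each tested at 5% would give up to 1 − 0.95³ = 14.3% if independent. Multiplicity across domains is a separate matter that this change does not settle.
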